### Patient and public involvement

This study is conducted in collaboration with the Swedish Partnership for Mental Health (NSPH). Patient and public representatives are not involved in issues surrounding study design, but are informed about and actively engaged in formulating research questions, determining outcomes and disseminating the results.

### Demographic variables

Demographic variables are recorded in the patients’ medical records through their social security number. These are age, gender, civil status and children. Psychiatric disorders are entered manually by healthcare providers using the Swedish version of the International Classification of Diseases and Related Health Problems, 10th Revision.

### Hospitalisation rates

Hospitalisation rates are recorded in the patients’ medical records when admitted to inpatient care or involuntary care (ie, when and how long each stay lasted). This consists of number of admissions and days in inpatient care, and number of admissions and days in involuntary care. All of the healthcare providers have been trained in how to enter this information in the system, including coding schemes specifically designed for this study in order to identify and track patients.

### Self-reported outcomes

Self-reported outcomes (ie, questionnaires) are collected after the patients have been assigned PCA and consented to take part in the research. For an overview, see table 1.

**Table 1 T1:** Overview of the self-reported outcomes

Self-report measure	Assessment				
	Assigned PCA	Monthly measures	12 months	24 months	36 months
Adults					
EQ5D-5L	X		X	X	X
WHODAS	X		X	X	X
CGI*	X		X	X	X
BBQ	X		X	X	X
GSE	X		X	X	X
GAD-7	X		X	X	X
PHQ-9	X		X	X	X
VAS	X	X	X	X	X
Adolescents					
KIDSCREEN	X		X	X	X
ASSIST-Y	X		X	X	X
C-GAS*	X		X	X	X
SDQ†	X		X	X	X
RCADS†	X		X	X	X

*Clinician-rating scale.

†Also completed by caregivers.

ASSIST-Y, Alcohol, Smoking and Substance Involvement Screening Test; BBQ, Brunnsviken Brief Quality of Life Scale; C-GAS, Children’s Global Assessment Scale; CGI, Clinical Global Impression; GAD-7, Generalised Anxiety Disorder-7 Items; GSE, General Self-Efficacy Scale; PCA, patient-controlled admissions; PHQ-9, Patient Health Questionnaire-9 Items; RCADS, Revised Children's Anxiety and Depression Scale; SDQ, The Strengths and Difficulties Questionnaire; VAS, Visual Analogue Scales; WHODAS, WHO Disability Assessment Schedule 2.0.

EQ5D-5L: A five-item questionnaire on current health status on the dimensions; mobility, self-care, usual activities (eg, family), pain/discomfort and anxiety/depression. Each item is scored in relation to a five-step scale, for example, ‘I am not anxious or depressed’ (1) to ‘I am extremely anxious or depressed’ (5). Furthermore, EQ5D-5L also includes a VAS on current health status; ‘worst imaginable health’ (0) to ‘Best imaginable health’ (100).^13^

WHO Disability Assessment Schedule 2.0: A 12-item questionnaire on overall physical and psychological well-being, for example, ‘In the past 30 days, how much difficulty did you have in: Taking care of household responsibilities?’. It is scored on five-point Likert-scale, ‘None’ (1) to ‘Extreme or cannot do’ (5). Three additional items also concern the number of days difficulties were present or interfered with daily living.^14^

Clinical Global Impression (CGI): A clinician-rating scale that asks healthcare providers to rate the health status of a patient at an initial assessment (referred to CGI-S); ‘normal, not at all ill’ (1) to ‘among the most extremely ill patients’ (7). The CGI is also used to determine the improvement of a patient (referred to as CGI-I); ‘very much improved since the initiation of treatment’ (1) to ‘very much worse since the initiation of treatment’ (7).^15^

Brunnsviken Brief Quality of Life Scale (BBQ): A 12-item questionnaire on the quality of life in six domains: leisure time, view of life, creativity, learning, friends and friendship, and myself as a person. Each domain is scored in accordance with satisfaction and importance, ‘do not agree at all’ (0) and ‘agree completely’ (4), which are then multiplied. The sum of the six products constitutes the total quality of life score.^16^

General Self-Efficacy Scale: A 10-item questionnaire on self-efficacy, that is, the belief to succeed in a given situation or task, for example, ‘I can always manage to solve difficult problems if I try hard enough’ (Item 1). It is scored on a four-point Likert scale, ‘not at all true’ (1) to ‘exactly true’ (4).^17^

Generalised Anxiety Disorder-7 Items: A seven-item questionnaire on symptoms of anxiety and worry, for example, ‘How often have they been bothered by the following over the past 2 weeks? Feeling nervous, anxious, or on the edge’ (Item 1). It is scored on a four-point Likert scale, ‘not at all’ (0) to ‘nearly every day’ (3).^18^

Patient Health Questionnaire-9 Items: A nine-item questionnaire on symptoms of depression and mood, for example, ‘How often have they been bothered by the following over the past 2 weeks? Little interest or pleasure in doing things?’ (Item 1). It is scored on a four-point Likert scale, ‘not at all’ (0) to ‘nearly every day’ (3).^19^

Visual Analogue Scales (VAS): Four items assessing different aspects of the patients’ care needs and current health status are administered monthly via SMS. These include the following: (1) ‘I feel confident about receiving care when I need it’, (2) ‘I am able to actively participate in my care’ and (3) ‘I believe care is available when needed’. These are scored on a continuum ranging from ‘I do not agree at all’ (0) to ‘totally agree’ (10). Also, a fourth item concerns ‘How would you rate your current health status?’, which is rated between ‘worst possible health’ (0) and ‘best possible health’ (10).

For adolescents and their caregivers, a separate set of self-reported outcomes will be used.

KIDSCREEN: An 11-item questionnaire on aspects related to health-related quality of life, for example, ‘Thinking about the last week: have you been able to do the things that you want to do in your free time?’ (Item 1). It is scored on a five-point Likert scale, ‘not at all’ or ‘never’ (0) to ‘extreme’ or ‘always’ (4). One item is supposed to reflect the participant’s overall health status, that is, ‘In general, how would you say your health is?’. KIDSCREEN is administered to both the patients and their caregivers.^20^

Alcohol, Smoking and Substance Involvement Screening Test: A seven-item questionnaire on alcohol, substance, and tobacco use among adolescents. It screens for the consumption and negative effects of different compounds, similar to AUDIT and DUDIT, weighting scores differently depending on frequency and impact of their use.^21^

Children’s Global Assessment Scale: A clinician-rating scale that asks healthcare providers to rate the health status of a patient. It is scored on a continuum ranging from ‘Needs constant supervision’ (1-10) to ‘Superior functioning’ (100).^22^

The Strengths and Difficulties Questionnaire (SDQ): A 25-item questionnaire on the psychological well-being of an adolescent, for example, ‘Often loses temper’ (Item 5). It is scored on a three-point Likert scale, ‘not true’ (0) to ‘certainly true’ (2). SDQ is administered to both the patients and their caregivers.^23^

Revised Children’s Anxiety and Depression Scale (RCADS): A 47-item questionnaire covering different symptoms of different psychiatric conditions, for example, ‘I worry that something bad will happen to me’ (Item 27). It is scored on a four-point Likert scale, ‘never’ (0) to ‘always’ (3). RCADS is administered to both the patients and their caregivers.^24^

A separate study will also investigate how the use of PCA among adolescents affect their caregivers’ quality of life (BBQ), functioning (Burden Assessment Scale),^25^ and the perceived reception by healthcare providers (Family Involvement and Alienation Questionnaire).^26^

### Sample size calculation

This study intends to examine the impact of introducing PCA in psychiatric care in Region Stockholm. As such, only patients who are assigned PCA and have consented to take part in the research are included. An a priori sample size calculation, which is typically used to estimate an adequate sample size for subsequent recruitment, is thus not informative. However, based on previous experiences of introducing PCA in the region, it is reasonable to expect about twelve patients per inpatient ward who consent to participate, which would amount to a total sample size of 564.^7^ When calculating the standardised effect size possible to detect under these circumstances, based on the difference between two dependent means, and using a probability level of 0.05 and a power of 0.80, the result is Cohen’s *d* of 0.12, which is a small, although clinically relevant effect for a population of patients with severe psychiatric disorders, and in line with similar findings on self-reported outcomes.^4 8 9^

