## Introduction

Patients with severe psychiatric conditions, such as schizophrenia spectrum disorders, borderline personality disorder and eating disorders, often have care needs that warrant frequent admissions to inpatient care. Historically, it has been up to the healthcare providers to decide who and when to admit, sometimes referred to as the gate-keeper model. In essence, patients may seek care on their own, but the final decision to permit admission has always been made by a physician.^1^ However, recent trends towards patient participation and shared decision-making in healthcare has questioned this practice.^2^ In particular, the concept of patient-controlled admissions (PCAs) marks a dramatic shift in authority and increased partnership in psychiatric inpatient care, whereby patients are given the possibility of admitting themselves when needed. The basic premise is to identify and grant PCA to those who might benefit the most from its use as a way of preventing deterioration and novel bouts of illness and support patient empowerment. The procedures differ somewhat between settings and patient groups, but typically involves three to five inpatient days per stay, with or without restrictions regarding the number of admissions allowed per month.^1^

The effects of PCA have been examined in several studies. Early attempts of implementation were done in the USA and Australia, but the first large-scale investigations were made in the Netherlands, Norway, Denmark and Sweden.^3–10^ In sum, research indicates an increase in the number of admissions to inpatient care, but a decrease in the number of days in inpatient care. Meanwhile, both the admissions to and days in involuntary care decrease, suggesting that patients admit themselves more often, but require less fewer admissions of shorter duration, in line with the idea of using PCA to promote independence and increase help-seeking behaviours. However, apart from hospitalisation rates, self-rated outcomes have been far less explored. Aspects such as recovery and well-being do not demonstrate any significant changes, but self-report measures have been few and mainly focused on general functioning.^4 8 9^ Yet, qualitative studies imply that PCA can be beneficial in terms of increasing autonomy, agency, and well-being among patients. This is evident even in those cases where admissions are seldom or never used, suggesting that it might constitute a safety net for those at risk.^11^

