PCA has been available since 2014 in Region Stockholm’s psychiatric care, which is Sweden’s largest hospital sector, but only for specific patient groups; schizophrenia spectrum disorders,^7^ eating disorders,^9^ and borderline personality disorder.^12^ Different procedures for using PCA have also been used depending on diagnosis, such as the length of each stay. However, following a resolution by the popularly elected Region Stockholm Assembly, the implementation of PCA will be completed in 2023 and involve patients with severe psychiatric conditions, irrespective of diagnosis, using the same procedures in the whole region. This will allow a large-scale implementation and evaluation of its effects, both in terms of hospitalisation rates and self-reported outcomes, up to 36 months following the assignment to PCA. A large number of patients with many different diagnoses will take part in several quantitative studies; including substance use, which has never been the subject to evaluation of PCA before. Furthermore, the use of additional self-report measures will permit an examination of its impact on symptoms, quality of life and autonomy. In addition, the implementation of PCA in child and adolescent psychiatry will be the first of its kind, making it possible to examine its potential effects among adolescents. Lastly, qualitative studies will examine the experiences of patients, caregivers of adolescents, and healthcare providers in an attempt to understand the use, and potential benefits and drawbacks of PCA. Overall, approximately 45 inpatient wards will eventually be included in this study, thus being, to the best of the authors’ knowledge, the largest attempt at defining the effects of PCA.

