## Method and analysis

### Setting

This study is placed within the psychiatric care of Region Stockholm, which is the largest hospital sector in Sweden, serving a population of two million citizens. It is organised as nine public healthcare clinics, and four private healthcare clinics. One of these clinics constitute child and adolescent psychiatry, two concern eating disorders and two are dedicated to substance use disorders. One additional clinic is reserved for forensic psychiatry, but because its patients have been sentenced to care, these are not eligible to receive PCA. The 13 clinics that are included consist of approximately 45 inpatient wards and about 120 outpatient units that work together as pairs (ie, more than one outpatient unit can share the same inpatient ward). Each inpatient ward will in turn designate at least one bed for PCA. The healthcare providers consist of medical doctors and nurses with or without specialist training in psychiatry, mental health workers, counsellors, psychologists, psychotherapists, social workers, physiotherapists, occupational therapists and students undergoing basic or advanced clinical training in the field of medicine or psychiatry. The starting date of this study was 1 January 2022, and the planned end date is 31 December 2027.

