### Study design

This study will evaluate the effects of PCA in Region Stockholm in collaboration with the Commissioner of Healthcare. This follows a resolution made by the popularly elected Region Stockholm Assembly, which means that both the implementation and policy surrounding PCA have already been decided. Hence, according to the decision, all patients with severe psychiatric conditions who are considered by their healthcare providers to have great care needs will be offered PCA as long as the criteria mentioned above are fulfilled. Furthermore, because the primary objective of the PCA programme is the provision of healthcare and not research, a more complex study design using randomisation on an individual or clinic level (ie, cluster) is not allowed due to ethical and judicial reasons. Hence, this study is restricted to a naturalistic prospective study design. Patients are followed for 12, 24 and 36 months using their medical records to check changes in hospitalisation prior to (pre) and following inclusion in the PCA programme (post), similar to what has been done previously.^7^ For example, patients who are included in November 2021 may have hospitalisation rates retrieved from the period November 2018–2020 and compared against hospitalisation rates from the period November 2022–2024, depending on the availability of historical data. In terms of self-reported outcomes, patients complete the measures when being assigned PCA and at the yearly follow-up assessments, with the exception for the VAS that is administered monthly via SMS. However, in these specific cases, historical data do not exist as these measures have not been collected previously. Only patients with no previous use of PCA when they consent to take part in this study will be analysed, as recorded in their hospital records.

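### The stated total of 564 does not follow from about 12 patients in each of about 45 wards (540), and the detectable d of 0.12 is a best case that no self-report scale in the plan can match

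*Protocol article*

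**What the plan says.** The Sample size calculation section explains that everyone assigned PCA who consents is included, so a prior calculation would not inform recruitment. It then gives an expected size: "about twelve patients per inpatient ward who consent to participate, which would amount to a total sample size of 564". From that total it derives a detectable Cohen's d of 0.12 for a paired comparison of means, at a probability level of 0.05 and a power of 0.80. It describes this as small but relevant to patients, and as consistent with earlier self-report results.

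On the number of wards, the Setting section says "The 13 clinics that are included consist of approximately 45 inpatient wards" and the Introduction says "approximately 45 inpatient wards will eventually be included in this study". The Abstract and the strengths and limitations list also give approximately 45.

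On the outcomes, the Self-reported outcomes section states: "For adolescents and their caregivers, a separate set of self-reported outcomes will be used". Table 1 confirms that no instrument appears in both the adult and the adolescent block. The Statistical analysis section expects skewed, heavy-tailed hospitalisation data, to be handled by non-parametric or bootstrap methods. It plans multilevel models for self-report, and multiple imputation or maximum likelihood for lost values.

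**The concern.** The total is given as an exact figure but does not equal the product of the two numbers it rests on. The detectable effect computed from it is the only precision statement in the article. The article presents it beside self-reported outcomes without saying that it needs the whole sample, complete and independent, on a single scale.

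What is at stake is how later results are read. If a self-report scale shows no clear change, a reader of the article could assume that the study had 80% power against d = 0.12 on that scale. The article's own design features mean that it would have had less. For hospitalisation, which is the primary question, the reader has no figure that can be turned directly into admissions or days.

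**Working it through.** **Inputs from the article.** About 12 patients per ward, total 564, level 0.05, power 0.80, paired means (Sample size calculation); approximately 45 wards (Abstract, strengths and limitations list, Introduction, Setting).

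**Inputs assumed here, for illustration only.** Loss of 30%; intraclass correlation (ICC) of change scores within ward of 0.02, 0.05 and 0.10. The article gives neither a loss rate nor an ICC.

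**1. The total.** 12 x 45 = 540. The stated figure is 24 higher, which is 24/564 = 4.3% of it. 564/12 = 47 wards exactly; 564/45 = 12.53 patients per ward.

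**2. The article's detectable effect.** For a paired comparison, d = (z for 0.975 + z for 0.80)/√n = 2.8016/√n.
- n = 564: 2.8016/√564 = 0.1180 (noncentral t: 0.1182).
- n = 540: 2.8016/√540 = 0.1206 (noncentral t: 0.1208).

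Both round to 0.12, so the article's figure reproduces. A one-sided test at 564 would give 0.105, so the figure is two-sided. Power at d = 0.12 is 81.2% with 564 and 79.5% with 540. Correcting the total therefore leaves the published d unchanged.

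**3. What 0.12 requires.** One test at 0.05, all patients contributing a complete pair, and no correlation between patients of the same ward. Set against the article:
- *Sample per scale.* Adults and adolescents complete different instruments, so each scale's n is below the total. The split is not given. If patients were spread evenly over the 13 clinics, one of which is child and adolescent psychiatry (an assumption), adult n would be 564 x 12/13 = 521, with d = 2.8016/√521 = 0.123. From 540 it would be 498, with d = 0.126.
- *Loss.* The Statistical analysis section expects lost values; the calculation allows for none. From 540, 30% loss leaves 378, and d = 2.8016/√378 = 0.144.
- *Ward clustering.* The expected total is built ward by ward, and patients of a ward share its PCA bed or beds (Procedure section). Only correlation of change within ward inflates a within-patient comparison.

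**4. Loss and clustering together, from 540.** 378/45 = 8.4 patients per ward. Design effect = 1 + (8.4 − 1) x ICC, and d = 2.8016 x √(design effect/378).

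| Assumed ICC of change | Design effect | Effective n | Detectable d |
|---|---|---|---|
| 0.02 | 1.148 | 329 | 0.154 |
| 0.05 | 1.370 | 276 | 0.169 |
| 0.10 | 1.740 | 217 | 0.190 |

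Power at d = 0.12 falls to about 59% in the first row and 42% in the last.

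**5. Hospitalisation.** The formula works in standard deviations of the paired difference. The article expects these data to be non-normal and plans other methods for them. It gives no standard deviation, so 0.12 cannot be converted into admissions or days.

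**The case against.** The best defence is that nothing depends on the slip. Both inputs are approximate, d is 0.12 either way, and the article sets no recruitment target. That stands, and it makes the arithmetic a minor correction.

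Stronger conclusions are tempting, and the document does not support them:

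- *That 0.12 is optimistic for every planned analysis.* Hospitalisation comes from medical records, where little may be missing. A bootstrap of paired means has about the power of a paired t-test. At 564 a signed-rank test would move d only to 0.121 for normal differences (efficiency 3/π) and to 0.127 at an efficiency of 0.864. Mixed models with covariates and repeated measures may gain power.
- *That prior PCA users must be subtracted from the total.* The Study design section says "Only patients with no previous use of PCA when they consent to take part in this study will be analysed", but the twelve per ward comes from experience of introducing PCA and may already mean new users.
- *That the Introduction contradicts the benchmark.* It reports of earlier work: "Aspects such as recovery and well-being do not demonstrate any significant changes". A true effect near 0.12 would often be non-significant in a small study, so the two statements can both be true. The cited studies are not available here. What remains is that the article gives no support for calling 0.12 relevant to patients.
- *That the four hospitalisation measures at three horizons show a multiplicity error.* The handling of multiplicity may sit in an analysis plan that is not shown, and it is a separate matter from this calculation.

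It can also be said that allowances for loss and clustering are usually left to the analysis plan. That is fair for the details. It does not cover a published figure presented for self-report without its conditions.

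**Conclusion.** The point holds in a limited form. The total of 564 does not follow from the stated ward count: 540 does, and 564 needs 47 wards. The effect on the detectable d is nil at two decimals (0.118 against 0.121).

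The d of 0.12 is arithmetically right for a single two-sided paired comparison with complete, independent patients. It applies to no self-report scale in the plan, because none is given to both adults and adolescents and because losses are expected. It does not directly describe the primary hospitalisation outcomes either.

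The size of the gap is uncertain. The adult restriction alone may be small (about 0.123 to 0.126 under an even spread over clinics). With 30% loss and an ICC of change of 0.02 to 0.10, d is about 0.15 to 0.19. Those two inputs are assumptions and not taken from the article, so the range shows a plausible order of magnitude and does not estimate what the study will achieve.

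**What to change.** - Reconcile the total with the ward count: either 540, or 564 with 47 wards stated consistently throughout.
- Either label 0.12 as the best case for one complete, unclustered, two-sided paired comparison, or restate it for adult self-report using the expected adult n, with the assumed loss and the assumed ward correlation of change given beside it.
- Say that the figure does not directly describe the hospitalisation outcomes.
- Support the claim of clinical relevance with a reason, or drop it.

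The cost is a few sentences and a slightly less favourable stated figure. No extra patients and no change of design or analysis are needed.
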